# The MenoStim Trial: Study Protocol for a Randomised, Sham-Controlled, Double-Blinded, Pilot Clinical Trial Exploring the Neurophysiological, Cognitive, Mood and Biochemical Effects Associated with Non-Invasive Brain Stimulation During the Menopause Transition

**DOI:** 10.1136/bmjopen-2025-106745

**Published:** 2025-12-19

**Keywords:** Cognition, Transcranial Magnetic Stimulation, Depression & mood disorders, Brain, Electroencephalography, Aging

## Abstract

**Introduction:**

Intermittent theta-burst stimulation (iTBS) is a non-invasive brain stimulation technique that has been shown to improve cognition and mood when applied to certain brain structures and regions. Despite research demonstrating that iTBS may have clinical utility in treating cognitive and mood changes, no study has yet been conducted to explore the potential to modulate the neurophysiological changes that can underpin cognitive and mood changes during the menopause transition. Cognitive and psychological symptoms are commonly reported by females experiencing the menopause transition, and it is thought that these symptoms arise due to various neurophysiological, metabolic and endocrinological changes. Despite being common, there is a lack of treatments available for managing these symptoms and a scarcity of data regarding the mechanisms by which they occur.

**Methods and analysis:**

The aim of this 5-week randomised, sham-controlled, double-blinded pilot clinical trial (n=72) is to assess the underlying mechanisms of action of iTBS in females in the late menopause transition and the relationship with cognition and mood. Data will be analysed using Stata^TM^. Normality checks will guide the choice between parametric and non-parametric tests. Generalised linear models will assess within-subject and between-subject effects across timepoints, with additional regression analyses exploring associations between biomarkers, cognition and mood. Effect sizes, CIs and relevant test statistics will be reported, with significance set at p<0.05.

**Ethics and dissemination:**

The study protocol has been reviewed and ethically approved by the Western Sydney University Human Research Ethics Committee (H16200; 8 November 2024). All participants will provide written informed consent prior to enrolment. Results from this trial will be disseminated via peer-reviewed publications and conference presentations, with findings shared in accordance with open science and data transparency principles.

**ANZCTR registration number:**

ACTRN12625000030471, Australian New Zealand Clinical Trials Registry

STRENGTHS AND LIMITATIONS OF THIS STUDYRandomised, double-blinded, sham-controlled design minimises bias and enhances internal validity.Multimodal assessments (electroencephalogram, transcranial magnetic stimulation, cognition, mood and biomarkers) capture both mechanistic and clinical effects.Clearly defined late-menopause transition criteria ensure a well-characterised sample.A matched sham coil reproducing the sound and scalp sensations of active stimulation maintains blinding integrity.Single-site pilot design with a small sample limits generalisability but supports feasibility assessment.

##  Introduction

### Background and Rationale

Menopause marks the permanent cessation of menstruation and is preceded by a midlife neuroendocrine shift known as the menopause transition. While vasomotor symptoms are the most reported and studied, there is limited research on managing other prevalent symptoms. This is significant, given that 62–67% of females report subjective cognitive complaints (SCCs) during this period, such as difficulties with concentration, memory, planning and ‘brain fog’.^1^ In addition, studies show objective impairments in working memory, verbal memory and executive function compared with reproductive-age females.^2^ Survey data also indicate that 47% of menopausal females report depression and 37% experience anxiety.^3^

Cognitive and psychological symptoms throughout the menopause transition are thought to stem from neurophysiological, metabolic and endocrinological changes. A recent multimodal neuroimaging study found that menopause negatively affects white matter structure, energy metabolism and connectivity in regions responsible for higher-order cognition.^4^ Another study reported reduced glucose metabolism in key cortical areas, correlated with decreased mitochondrial cytochrome C oxidase activity in peri-menopausal and postmenopausal females.^5^ Preclinical findings further show that the shift to irregular menstrual cycling is marked by reduced bioenergetic gene expression, impaired glucose metabolism, mitochondrial dysfunction and diminished long-term potentiation.^6^ Electroencephalogram (EEG) studies have identified distinct changes in brain activity during the menopause transition. Elevated beta power during sleep in late-transition and postmenopausal females indicates hyperarousal and poor sleep quality.^7^ These data support the hypotheses that targeting brain bioenergetics and neurocognitive changes may be the key to developing novel treatments for menopause-related symptoms.

The International 2023 Practitioner’s Toolkit for Managing Menopause notes the most robust Clinical Practice Guidelines support menopausal hormone therapy (MHT) as the most effective treatment to improve vasomotor symptoms. Recent data suggest that it is still unclear whether MHT can result in improved cognitive function in midlife women due to insufficient evidence.^8^ MHT is also associated with specific adverse drug reactions and is contra-indicated in some oestrogen-dependent cancers.

The limited treatment options for managing cognitive and psychological symptoms of menopause, along with potential side effects of MHT, have driven interest in non-pharmacological alternatives that can target neurophysiological changes. Repetitive transcranial magnetic stimulation (rTMS), a non-invasive technique that uses electromagnetic fields to stimulate cortical activity, has shown promise in the treatment of psychiatric and neurological disorders. rTMS applied to certain brain regions and structures has been shown to improve cognition and mood. The dorsolateral prefrontal cortex (DLPFC) is a core region involved in executive functions including attention, working memory and emotional regulation, and so has become an area of interest in the management of cognitive and psychological symptoms. Two meta-analyses have shown that high-frequency rTMS over DLPFC can significantly improve global cognitive function.^9 10^ Systematic reviews and meta-analyses support the efficacy and acceptability of rTMS over DLPFC for treating depression.^11 12^ The non-invasive nature of rTMS and its low side effect profile suggests that the intervention may be of high clinical utility for treating the cognitive and mood symptom profiles in menopause.

Although rTMS has shown acceptable efficacy, remission and dropout rates, its standard daily treatment schedule presents feasibility challenges. Protocols typically require 10 or more 20–40-min sessions per week over several weeks, which can be time-consuming and burdensome. These practical demands, along with delays in symptom improvement, pose limitations for clinical trial recruitment and retention. Such limitations may be ameliorated through the use of theta-burst stimulation (TBS) protocols, which represent a rapid form of rTMS, which have been shown to up-regulate or down-regulate excitability in the cortex by mimicking the natural neuronal firing pattern frequencies of the brain.^13^ Preliminary research suggests that intermittent patterns of TBS (iTBS) can induce changes in cortical activity comparable to traditional rTMS in a fraction of the time (40–190 s per session). Further, recent systematic reviews have shown that iTBS can improve cognition in healthy people and people with neurological disorders^14^ and mood in people with depressive disorders.^15^

### Objectives and Trial Design

Despite research demonstrating that iTBS may have clinical utility in treating cognitive and mood changes, no such study has been conducted to explore the potential of iTBS to modulate the neurophysiological changes that can underpin cognitive and mood changes during the menopause transition. Such data are essential in identifying potential mechanisms by which to treat or prevent cognitive decline during this transition. The objective of this randomised, sham-controlled, double-blinded pilot clinical trial is to assess the underlying mechanisms of action of iTBS in females in the late menopause transition and to assess the relationship with cognition and mood.

A pilot trial design was selected due to the novelty and exploratory nature of the research question; and to assess the intervention mechanisms to determine whether the protocol will be viable in future studies that would explore treatment efficacy as the primary outcome.

## METHODS AND ANALYSIS

### Study Setting

This research will be conducted in an academic setting. Study sites include the NICM Health Research Institute, Western Sydney University (Westmead NSW 2145, Australia).

### Patient and Public Involvement (PPI)

A public involvement group was formed consisting of cognitive neuroscientists, neuropsychologists, analytical biochemists, physiotherapists and GPs experienced in cognitive assessments, TMS interventions and the management of menopause symptoms. The study methods were refined by input gained through discussions with these professionals. Females with lived experience of the menopause transition were consulted and helped with refining the study methods and participant resources. Advocacy groups, such as the Australasian Menopause Society, will provide support for recruitment and dissemination via newsletters, websites and social media. Consumers (e.g., females experiencing the menopause transition) will be consulted in the writing of lay summaries for dissemination of the trial findings to relevant patient, community and clinical groups.

### Inclusion and Exclusion Criteria

This pilot clinical trial will recruit females in the late menopausal transition stage (Stage −1 according to the STRAW+10 Criteria^16^). This cohort was chosen for two primary reasons: (a) there is evidence to suggest that the cognitive deficits reported are most pronounced during the late menopause transition and can normalise in the postmenopause period^17^; and (b) rTMS treatment responsivity in females with mood disorders is associated with a higher oestradiol/progesterone ratio.^18^ Inclusion and exclusion criteria are summarised in box 1.

Box 1Inclusion and Exclusion CriteriaInclusion CriteriaFemales aged between 45 to 55 years who are undergoing the late menopausal transition stage according to the STRAW criteria as defined by: (a) amenorrhoea of 60 days or longer; (b) follicle-stimulating hormone (FSH) levels greater than 25 IU/L in a random blood draw and (c) self-reported vasomotor symptoms.Females experiencing self-reported subjective cognitive complaints relative to previously normal cognitive status.Willing to complete all study-related activities for the complete trial, including in-person assessments and remote follow-ups.Exclusion CriteriaIndividuals who have contraindications to TMS.Reproductive age females; females in the late reproductive stage or the early menopausal transition and postmenopausal females.Females who have been receiving MHT treatment for less than 3 months at the time of recruitment or plan to commence MHT treatment during the study duration.Individuals using neuroactive medications, including anticonvulsants, antidepressants and anxiolytics.A diagnosis of neurodegenerative, psychiatric affective, non-affective or neurological illness.Significant cognitive impairment as deemed by scoring 17 or less on the Telephone Montreal Cognitive Assessment (T-MoCA).Current episode of major depression as deemed by scoring 15 or greater according to the Patient Health Questionnaire-9 (PHQ-9).High dependence on medical care due to past or current medical conditions.Study physician discretion regarding medical status, appropriateness of participation or concern about intervention adherence.Individuals who are not willing to follow the study protocol, eg, are not able to attend face-to-face visits or those who plan to move out of the area within the treatment period.Individuals who are actively participating in another clinical trial(s).Individuals who are not proficient in reading and writing in English.

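### Box 1 lets established MHT users enter but stages them by the same three signs as non-users, which are less reliable under MHT, and the stated allocation does not balance MHT use

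*Protocol article*

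**What the plan says.** All of this is in the protocol article.

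- **MHT rule (Box 1, exclusion criteria).** The excluded group is "Females who have been receiving MHT treatment for less than 3 months at the time of recruitment or plan to commence MHT treatment" during the study. Use of 3 months or longer is not excluded.
- **Staging rule (Box 1, inclusion criteria).** Every entrant needs (a) "amenorrhoea of 60 days or longer", and (b) and (c) "follicle-stimulating hormone (FSH) levels greater than 25 IU/L in a random blood draw and (c) self-reported vasomotor symptoms". The three are joined by 'and'. Earlier stages and postmenopausal women are excluded. No separate rule is given for MHT users.
- **MHT and vasomotor symptoms (Background and Rationale).** Guidelines are said to "support menopausal hormone therapy (MHT) as the most effective treatment to improve vasomotor symptoms".
- **Reason for the cohort (Inclusion and Exclusion Criteria).** One of two reasons is that "rTMS treatment responsivity in females with mood disorders is associated with a higher oestradiol/progesterone ratio".
- **Claimed strength (Strengths and Limitations).** "Clearly defined late-menopause transition criteria ensure a well-characterised sample".
- **Allocation.** 2:1, permuted blocks of 6, run in REDCap. No stratification factor is named.

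**The concern.** The staging signs are meant to show where a woman stands in her natural transition. The article says that MHT relieves one of them, yet it requires that sign of women on MHT. That oestrogen also lowers FSH, and that the regimen shapes bleeding, is general pharmacology which the article does not state. The point does not rest on it alone.

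Three things are at stake. The trial's question is confined to the late transition, and stage is less certain in users. The article treats hormonal state as relevant to rTMS response, and MHT changes that state. The sham arm has only 24 women, so the arms can differ by chance in a background factor that the authors themselves consider relevant.

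**Working it through.** **1. The criteria applied to an established user.**

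| Sign in Box 1 | Effect of MHT | Source | Likely error in a user |
|---|---|---|---|
| Amenorrhoea of 60 days or longer | Regimen shapes bleeding | General pharmacology | Amenorrhoea may reflect the regimen; the line to postmenopause is also blurred |
| FSH above 25 IU/L, one random draw | Tends to lower FSH | General pharmacology | A late-transition woman may be screened out |
| Self-reported vasomotor symptoms | Relieves them | Background and Rationale | A late-transition woman may be screened out |

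Two of the three errors are false exclusions. Only the first can help a woman in wrongly, and she must still meet the other two.

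**2. Chance imbalance in MHT use.** Inputs: 72 women in total (Sample Size Determination), and 2:1 allocation, hence 48 active and 24 sham. The share of users is not stated; 10%, 20% and 30% are assumed, which gives K = 7, 14 and 22 users.

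If x users fall in the sham arm, the difference in proportions is x/24 − (K − x)/48 = (3x − K)/48. A difference of 15 points or more needs |3x − K| ≥ 7.2; 10 points or more needs |3x − K| ≥ 4.8. Without stratification, x is hypergeometric (72 women, K users, 24 drawn).

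| Assumed share | K | x giving 15 points or more | Probability | Probability of 10 points or more |
|---|---|---|---|---|
| 10% | 7 | 5 or more | 0.037 | 0.212 |
| 20% | 14 | 2 or fewer, 8 or more | 0.121 | 0.359 |
| 30% | 22 | 4 or fewer, 10 or more | 0.180 | 0.421 |

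The expected number of sham-arm users is K/3, or about 2, 5 and 7. That is too few to study the two hormonal states separately afterwards.

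**3. What an imbalance does to an estimate.** Assume that MHT shifts an outcome by 0.5 SD. A 15-point imbalance moves the arm difference by 0.15 × 0.5 = 0.075 SD. The standard error is √(1/48 + 1/24) = 0.25 SD. Pooling users and non-users multiplies the variance by 1 + q(1 − q) × 0.5², which is 1.02, 1.04 and 1.05 at q = 10%, 20% and 30%.

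**4. Effect of stratifying.** Keep blocks of 6 (4 active, 2 sham) within each MHT stratum. Only the last block of a stratum can be incomplete, so x is 2–3 for K = 7, 4–6 for K = 14 and 6–8 for K = 22. At 48:24 the largest differences are |3 × 3 − 7|/48 = 4.2 points, |3 × 6 − 14|/48 = 8.3 points and |3 × 6 − 22|/48 = 8.3 points. None reaches 10.

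**5. Precision in non-users only.** The detectable standardised difference (two-sided 0.05, 80% power) is (1.960 + 0.842) × √(1/24 + 1/48) = 0.70 for all 72 women. With 65, 58 and 50 non-users at 2:1 it is 0.74, 0.78 and 0.84.

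**The case against.** The best defence is that this is a stable-background rule. Recent starters and planned starters are out and established users are in, which limits hormonal change over a 5-week study and helps recruitment to an exploratory pilot. That is coherent, and it stands as a reason for admitting users. It does not make the entry signs easier to interpret, nor users and non-users hormonally alike.

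Second, the effect on the arm comparison is small. Randomisation protects it in expectation, step 3 shows a modest shift, and baseline measurement with within-subject comparison removes part of any stable background difference. This stands for a shift in level. It does not cover the case in which MHT changes the response to stimulation, which no figure here quantifies.

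Third, the hormone-ratio finding is reported in females with mood disorders, while Box 1 excludes affective illness. So it explains the choice of cohort and does not show effect modification in this sample.

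Fourth, covariates and sensitivity analyses are commonly left to a full protocol or SAP. Their absence from the article is not held against it here; they appear only as part of the remedy.

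A reader might go further and infer that users cannot be staged at all, or that every enrolled user has an uninterpretable stage. The documents do not support this. The rule can be applied to users, all three signs are required together, and the stated effect on symptoms works towards excluding users. The counts of 7, 14 and 22 come from an assumed share, which the screening effect could make smaller, and nothing shows that any of these women would be misclassified. Nor is there ground to claim added noise in a vasomotor endpoint: Table 1 lists no dedicated one, only a menopause quality-of-life scale.

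**Conclusion.** The point holds as a moderate weakness that is cheap to improve. Box 1 admits established MHT users, applies unadapted staging signs to them, and so does not fully support the claim of a well-defined cohort or fit easily with the hormone-ratio rationale. The cost is heterogeneity, a less sharp target population and chance imbalance, not systematic bias between arms. At an assumed 10% to 30% of users among 72 women, an imbalance of 15 points or more has a probability of about 4% to 18%, and one of 10 points or more about 21% to 42%. These figures depend wholly on the assumed share and on an unstratified 48:24 split. The vasomotor link is stated in the article; the links to FSH and bleeding are general pharmacology.

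**What to change.** The trial team should reconcile the MHT criterion in Box 1 with the three staging criteria, the cohort rationale in the same section and the statement in Strengths and Limitations. Which MHT rule is right is for the team.

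If established users stay eligible:

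1. Stratify the REDCap allocation by current MHT use (yes/no), which is known at screening.
2. Include that factor as a covariate in the co-primary EEG and SICI/LICI models.
3. Report the co-primary estimates in non-users as a sensitivity analysis.

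The cost is one stratum, one model term and a less precise non-user estimate (detectable difference 0.74 to 0.84 SD instead of 0.70 SD under the assumed shares). An incomplete last block in each stratum can also move the total slightly away from 48:24.

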### Intervention

Participants will receive five sessions of iTBS over the left DLPFC. iTBS will be delivered using a MagVenture Pro x100 including MagOption (MagVenture, Ferum, Denmark). The coil will be held tangential to the scalp with the handle pointed posterolaterally away from the midline at 45 degrees to induce a second phase current in the posterolateral to anteromedial direction.^19^ The TMS coil will be positioned through a Brainsight neuro-navigation system (Rogue Research Inc., Canada) based on anatomical landmarks in MNI space.^20^ The coil will be positioned over the left dorsolateral prefrontal cortex (DLPFC) in accordance with the BeamF3 algorithm.^21^ A fixed, multi-hinge, TMS coil armature will be used to maintain accurate coil positioning during the intervention. The coil location and orientation will be monitored throughout the procedure using the Brainsight neuro-navigation system.

Bipolar surface electrodes (Ag/AgCl) will be used to record electromyographic (EMG) activity and determine the resting motor threshold (rMT). The active electrode will be placed over the first dorsal interosseous muscle of the right hand, and the ground electrode will be placed over the right olecranon. Electromyographic signals will be amplified (32,000), band-pass-filtered (20–1000 Hz) and sampled at 2 kHz using a Power 1401 Data Acquisition System and Signal3 software (Cambridge Electronic Design, Cambridge, UK). Participants will be seated with their right arm placed on forearm pronation and elbow flexion on a pillow across their lap. rMT will be determined as the lowest stimulation intensity at which 5 out of 10 stimuli delivered to the hotspot evoked a peak-to-peak MEP of at least 0.05 mV in the resting muscle. Stimulation intensity will be delivered at 90% of the rMT, which will be assessed at the start of each iTBS session.^22^

Active treatment will consist of five sessions of iTBS over five consecutive days. On every treatment day, participants will receive five blocks of iTBS, and each block will be separated by 10 minutes.^23^ Bursts of three pulses will be delivered at 50 Hz, repeated at 200-ms intervals in trains of 2 s.^23^ 2-s trains of iTBS will be repeated every 10 seconds for a total of 600 pulses per block and 3000 pulses per session.^23^

Sham will be delivered using a dedicated sham coil that reproduces the audible clicks and superficial somatic sensations of active stimulation, without delivering magnetic pulses to the cortex. The set-up will be handled by a blinded laboratory technician, and active and sham groups will receive identical information and instructions.

### Outcomes

All outcomes were assessed at three time points and full details of the outcome measures are outlined in table 1. As this is a pilot clinical trial, primary outcomes are mechanistic and include cortical activity, assessed via electroencephalography (EEG). Paired-pulse TMS will be used to investigate activity within intracortical circuits as a co-primary outcome. Intracortical inhibition will be measured via short-interval intracortical inhibition (SICI) and long-interval intracortical inhibition (LICI).

**Table 1 T1:** Schedule of Activities

Activity	Online Screening	Phone Screening	Baseline	Endpoint	Follow-Up
Inclusion and Exclusion Criteria	X	X			
FSH Pathology		X			
TMS Adult Safety Screen Questionnaire		X			
Telephone Montreal Cognitive Assessment		X			
EEG Measures			X	X	X
TMS Measures			X	X	X
Heart Rate Variability			X	X	X
Skin Conductance			X	X	X
Saliva Collection			X	X	X
Urine Collection			X	X	X
Memory and Cognitive Confidence Scale			X	X	X
Rey Auditory Verbal Learning Test			X	X	X
D-KEFS Verbal Fluency			X	X	X
Symbol Digit Modality Test			X	X	X
Paced Serial Addition Test			X	X	X
Conners Continuous Performance Test-3			X	X	X
Visual Analogue Scale to Evaluate Fatigue Severity			X	X	X
Patient Health Questionnaire-9		X	X	X	X
General Anxiety Disorder-7			X	X	X
Pittsburgh Sleep Quality Index			X	X	X
Menopause-Specific Quality of Life			X	X	X

D-KEFS, Delis-Kaplan Executive Function System; EEG, Electroencephalogram; FSH, Follicle Stimulating Hormone; TMS, Transcranial Magnetic Stimulation.

Secondary outcomes include changes in subjective cognitive complaints and objective changes in verbal memory, verbal learning, verbal fluency, psychomotor processing speed, working memory, and sustained attention and vigilance. The clinical trial will also assess the effects of an rTMS intervention on the psychological symptom profile as secondary outcomes, including depressive mood, anxiety, sleep quality, and quality of life.

Tertiary outcomes include changes in autonomic function, which will be assessed via skin conductance and heart rate variability (HRV). Changes in inflammatory and energetic markers and neuroactive metabolites will be measured via saliva and/or urine analysis.

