### Data Collection Methods

#### Electroencephalogram

Participants will be seated in an air-conditioned and sound-attenuated room with a built-in Faraday cage. Data will be acquired using the Compumedics Okti 32-channel acquisition module (Victoria, Australia), a high-definition portable EEG amplifier. Participants will be fitted with Okti EEG recording equipment and seated approximately 80 cm from a 21-inch screen with a keyboard placed in front of them. Electrodes will be positioned according to the international 10–20 montage system, covering locations including Fp1, Fpz, Fp2 and AF3, through to O2. Participants will first complete a brief electrooculogram (EOG) calibration task that will later be used for removal of EOG-related artefacts in the data.^25^ For resting-state, participants will be instructed to focus on a grey cross centred on a black background, measuring 10×10 mm, to record with their eyes open followed by eyes closed resting-state EEG for 6 min each.^26^ In both the EOG calibration and the resting-state, continuous electrophysiological data from 0 to 70 Hz will be recorded using the Compumedics CURRY nine digital signal-processing system (Victoria, Australia), referenced to Cz during active recording. Data will be digitised at 256 Hz.

Resting-state EEG data will be post-processed with standardised pipelines.^27^ Following this, aperiodic pink noise activity will be obtained due to its association with ageing and executive function and is hypothesised to reflect underlying neurobiological processes including neural spiking rates and excitatory-inhibitory balance.^28^

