#### Transcranial Magnetic Stimulation (TMS)

SICI and LICI will be studied using a paired-pulse technique that employs a conditioning-test design. The test stimulus will be adjusted to evoke a motor-evoked potential (MEP) of 1 mv amplitude in the first dorsal interossei muscle of the right hand.^29^ To measure SICI, the conditioning stimulus (CS) will be adjusted at 90% of the RMT, and multiple interstimulus intervals (ISIs) will be employed. ISIs include 1, 2, 3 and 5 ms for SICI. LICI will be investigated by implementing two supra-threshold stimuli, and the CS will be adjusted at 120% of the rMT. ISIs include 50, 100 and 150 ms.^29^

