### Statistical Methods

A data-driven approach will be applied to de-identified data in Stata^TM^ (StataCorp, Texas, USA). Normality checks will be performed for all variables via visual inspection of histograms to determine whether parametric or non-parametric approaches should be used. Two-tailed independent group *t*-tests with equal variances assumed will be used for all continuous variables, and χ^2^ tests will be conducted for categorical variables. Dependent variables taken at baseline and all following timepoints will be analysed for within-subject and between-subject comparisons using generalised linear models with planned simple contrasts for the within-subjects factor of time. To determine the relationship between immunological, bioenergetic and neuroimmune biomarkers and changes in cognition and mood, a logistic regression analysis will be performed.

A possible signal of efficacy will be explored via effect-size estimates of changes in tertiary outcomes (cognition and mood). Effect sizes, means, SDs and CIs will be reported. Normality checks will be performed, and data will be transformed if necessary. Where appropriate, parametric tests will be applied. A generalised linear model with fixed and random effects will be applied for the tertiary outcomes. Variables will include the between-subjects factor of group (active vs sham) and within-subjects factor of time (baseline, endpoint and follow-up). Pearson correlation coefficients (or their non-parametric counterpart) or multivariate regression involving tertiary outcomes will be conducted. All tests will be carried out one-tailed and using an alpha level of 0.05.

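### The co-primary outcomes are two measurement modalities with no chosen variable, visit or success rule, yet every test is set at 0.05: up to about 18 comparisons can bear on the primary claim

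*Protocol article*

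**What the plan says.** The Outcomes section of the protocol article names EEG-assessed cortical activity as primary, in wording that leaves the list open. It continues: "Paired-pulse TMS will be used to investigate activity within intracortical circuits as a co-primary outcome". It places SICI and LICI inside that second co-primary, and it has all outcomes measured at three time points. Participant Timeline gives these as Day 1, Day 5 and Week 5.

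The data collection sections multiply what each modality yields:

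- **SICI:** "ISIs include 1, 2, 3 and 5 ms for SICI".
- **LICI:** "ISIs include 50, 100 and 150 ms".
- **EEG:** recorded with "eyes open followed by eyes closed resting-state EEG for 6 min each". The Electroencephalogram section singles out aperiodic activity as the feature to be derived.

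On error control, the Abstract sets significance at p<0.05. Statistical Methods plans generalised linear models with simple contrasts over time and ends: "All tests will be carried out one-tailed and using an alpha level of 0.05". The opening paragraph of the same section specifies two-tailed t-tests.

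**The concern.** A primary outcome should tell the reader in advance which result will be read as the answer. Here the primary level is two families of measurements. Nothing ranks the intervals, the eyes conditions or the two post-baseline visits. The article does not say whether one positive result is enough or whether both modalities must succeed. A flat 0.05 is attached to whatever tests are run, so any member of either family could be reported as a positive primary finding.

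This matters even in a pilot. Objectives and Trial Design says the mechanistic assessment is meant to show whether the protocol is viable for later efficacy studies. The Discussion limits conclusions about efficacy but not about mechanism, and it envisages subgroup analyses of the mechanistic outcomes. A chance finding on mechanism could therefore feed into the case for the next trial.

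**Working it through.** The article states no family-wise error rate and no number of primary tests, so it has no figure of its own to reproduce on this point.

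**1. Count of comparisons, if everything listed is tested separately**

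Inputs: 4 SICI and 3 LICI intervals (Transcranial Magnetic Stimulation section), 2 eyes conditions (Electroencephalogram section) and 2 post-baseline visits (Participant Timeline). Assumption: one EEG measure per condition, with no channel-level testing.

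- Measures: 4 + 3 + 2 = 9
- Comparisons: 9 × 2 = 18

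If intervals and eyes conditions are pooled to one measure each for EEG, SICI and LICI, the count is 3 × 2 = 6.

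**2. Chance of at least one false positive with no true effect, independent tests**

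Formula: 1 − 0.95^k. It is the same for one-sided and two-sided tests.

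- k = 2: 1 − 0.95² = 9.8%
- k = 6: 1 − 0.95⁶ = 26.5%
- k = 9: 1 − 0.95⁹ = 37.0%
- k = 18: 1 − 0.95¹⁸ = 60.3%

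**3. The same chance with correlated tests**

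The test statistics are taken as normal with a common correlation. The document gives no correlations, so these are assumptions. Both sidednesses are shown because Statistical Methods states both.

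| Assumed correlation | 18 tests, two-sided | 18 tests, one-sided | 6 tests, two-sided | 6 tests, one-sided |
|---|---|---|---|---|
| 0 | 60% | 60% | 26.5% | 26.5% |
| 0.3 | 51% | 42% | 24% | 22% |
| 0.5 | 40% | 33% | 21% | 19% |
| 0.7 | 28% | 23% | 16% | 15% |

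A more structured assumption for the 18 tests has correlation 0.3 to 0.8 within EEG, SICI and LICI, 0 to 0.2 between them, and 0.5 to 0.7 between visits. It gives 40% to 56% two-sided and 37% to 52% one-sided.

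**4. Price of testing two named endpoints with Holm**

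Inputs: 60 analysed (Sample Size Determination), 2:1 allocation (Allocation), hence 40 and 20; 80% power, two-sided.

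Normal approximation: d = (z for alpha + z for power) × √(1/40 + 1/20), where the root is 0.274.

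- Alpha 0.05: (1.960 + 0.842) × 0.274 = 0.77 SD
- Alpha 0.025 (first Holm step): (2.241 + 0.842) × 0.274 = 0.84 SD

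The exact calculation with the noncentral t distribution (58 degrees of freedom) gives 0.780 and 0.863 SD. These are the figures used below.

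**The case against.** The strongest reply is that 18 is not a number in the article. The interval and eyes-condition lists describe how data are acquired, and they are not a list of hypothesis tests. The planned models could pool intervals or use one group-by-time test, which would give roughly 2 to 9 tests. This stands. A reader might infer that there are at least 18 tests, but the documents do not support that. Eighteen is what results if everything listed is tested separately.

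A reader might also infer that a false mechanistic finding is likely. That does not follow either. The probability exceeds one half only with all 18 tests and weak dependence, and these measures come from the same people, circuits and visits. With a common correlation of 0.5, or with pooling to six tests, it is below one half.

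A third reply is that a multiplicity method may be in an analysis plan that is not shown, and that co-primary may mean both modalities must succeed. The absence of a method is indeed no finding in itself. If both modalities had to succeed, there would be no inflation between them, but the free choice within each would remain. The point rests on what the article does fix: a primary outcome named only by modality, with a stated 0.05 for significance. The one-tailed sentence closes the paragraph on tertiary outcomes and could be read as limited to them. However, it is worded to cover all tests, and the p<0.05 in the Abstract is general.

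Finally, the trial is a pilot, it promises effect sizes and intervals, and no passage makes the decision on a later trial depend on a single p-value. That lowers the stakes. It does not remove the defect, because the article still sets a significance threshold for its results.

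**Conclusion.** The point holds in a limited form. The primary outcome is badly fixed, and the error rule attached to it does not control false positives across the comparisons it admits. The size depends on choices that the article leaves open:

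- **Separate testing, one EEG measure (18 tests):** up to 60% if independent; about 28% to 51% two-sided, or 23% to 42% one-sided, at assumed correlations of 0.7 to 0.3.
- **Pooled to EEG, SICI and LICI at two visits (6 tests):** about 15% to 26.5%, across correlations of 0.7 to 0 and both sidednesses. That is still about three to five times the nominal 5%.

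All correlations are assumptions. Channel-level EEG tests or further aperiodic parameters would raise the count, and joint modelling would lower it. The correction should be made, but the point does not undermine the trial's design.

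**What to change.** Before unblinding, the investigators should name one EEG variable in one eyes condition and one paired-pulse variable, both at one visit. A summary across intervals is one option for the paired-pulse variable, but the choice is theirs. Test the two with Holm at an overall 0.05, state the sidedness once, and say that success on either is judged under that procedure. Report all other intervals, conditions, visits and mechanistic measures as estimates with confidence intervals and no significance claim.

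A simpler alternative is to label the whole mechanistic set exploratory, report every estimate with its interval, and make no significance claims.

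No new data or participants are needed. Under the Holm option, with 40 and 20 analysed, the two-sided detectable difference at the first step rises from about 0.78 to 0.86 SD, and the remaining intervals and visits become exploratory. Narrowing a registered and ethically approved primary outcome may also require an update to the registration and the ethics record.
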